### Randomisation and allocation

The trial statistician will prepare a computer-generated random allocation sequence using R-coding, with blocks of random size stratified by clinic, allocating newborns to one of two study arms:

Arm 1: Labinic synbiotic every day for 10 days and then weekly to age 6 months.Arm 2: control group, usual care with no supplement.

Participants (infants) will be allocated at a ratio of 1:2 in the intervention and control arms, respectively. The allocation sequence will be held by an independent pharmacist in Senegal who will prepare sequentially numbered, sealed, opaque envelopes according to the random allocation sequence. The random allocation sequence will be concealed from all other members of the research team including staff allocating newborns to the trial arms and laboratory staff analysing the biological samples. Each envelope will be opened sequentially following recruitment of each newborn and will contain a card indicating the trial arm. The trial arm will then be linked to the infant’s unique AASH identification number. Mothers/carers who decline for their infant to participate in the SENGSYN study will continue in the AASH observational cohort.

Following participant allocation, study staff will assist the mother/carer in administering the first dose of the synbiotic to infants in the intervention arm.

### Intervention

The trial will explore the impact of the Labinic synbiotic, composed of a prebiotic (BENEO Orafti Synergy1; 50% oligofructose/50% fructooligosaccharide, 200 mg) plus three live bacterial strains (*Lactobacillus acidophilus* NCFM, *Bifidobacterium infantis* Bi-26 and *B. bifidum* Bb-06; total of 5 billion organisms/dose (Biofloratech, Walton-on-Thames, Surrey, UK). The synbiotic supplement is a powder in capsules with one dose per capsule. The contents of the capsule can be sprinkled directly into the infant’s open mouth before feeding. Study staff will visit daily for 9 days after the initial dose and then weekly to age 6 months (32 doses in total) to supervise the administration of the synbiotic and record adherence. Administration will be repeated once if the infant vomits within 30 min of synbiotic administration. In infants taking antibiotics, including HIV-exposed infants taking daily co-trimoxazole, the synbiotic will be administered where possible at least 4 hours before/after the antibiotic or between doses to minimise the effect of the antibiotic on the synbiotic microbes. Antibiotic usage will be recorded during dosing visits and morbidity follow-up. Infants randomised to the control arm will receive the same follow-up as infants in the AASH observation cohort. All infants will receive routine care as per national guidelines and will have contact details and mobile phone numbers of study staff for assistance in case of infant illness.

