## Methods and analysis

### Trial design

Senegal Synbiotic (SENGSYN) is an individually randomised, two-arm, open-label, controlled trial. The protocol for this trial has been developed in accordance with the Standard Protocol Items: Recommendations for Interventional Trials guideline. The trial is part of the research conducted within the UK Research and Innovation Global Challenges Research Fund (UKRI GCRF) Action Against Stunting Hub (AASH) (https://actionagainststunting.org/), an interdisciplinary research consortium investigating the precursors of child stunting to inform programmes and policies to reduce the global burden of this condition. Infants born to women recruited during pregnancy in Kaffrine, Senegal in the AASH observational study will be assessed for eligibility and recruited to participate in the SENGSYN trial.

Recruited infants will be randomised to receive either a daily supplement of a synbiotic in the first 10 days of enrolment and then weekly up to 6 months of age, or no intervention, with the children followed up to 24 months of age. Detailed anthropometry will be conducted at birth and months 3, 6, 12, 18 and 24; stool samples will be collected at 1, 6 and 24 months; and blood samples will be collected at 6 and 24 months. Assessments of morbidity and breast feeding are conducted weekly up to 24 months of age (table 1).

**Table 1 T1:** Schedule of enrolment, intervention and assessments

	Study period										
	Enrolment/allocation	Post allocation									Close-out
Time point	Birth	1 month	2 months	3 months	4 months	5 months	6 months	9 months	12 months	18 months	24 months
Enrolment											
Eligibility screen	X										
Informed consent	X										
Random allocation	X										
Intervention											
Intervention arm		Synbiotic daily for 10 days then weekly until 6 months									
Control arm		Routine care									
Assessments											
Weekly morbidity diary		X	X	X	X	X	X	X	X	X	X
Body weight, breast feeding	X	X	X	X	X	X	X	X	X	X	X
Other anthropometry		X		X			X	X	X	X	X
Stool pathogens/microbiota/ biomarkers		X					X				X
Blood biomarkers							X				X
Epigenetic status in saliva		X									X

The trial follows the Standard Protocol Items: Recommendations for Interventional Trials protocol.

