### Outcomes

All infants will be followed up to 24 months of age with anthropometry, biological sample collections (blood, stool and saliva), and morbidity assessment conducted at scheduled time points (table 1).

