Infants who develop adverse events that may be due to the study intervention will be identified by parents/carers contacting study staff or at follow-up visits. If appropriate, participants will be referred to the hospital for evaluation and treatment according to local guidelines. In the case of a serious adverse event (SAE), subjects will be referred to an appropriate health facility for management. All SAEs will be reported to the in-country principal investigator or an assigned representative within 24 hours of the research staff becoming aware of it. The information reported will include the nature of the event, date of onset, severity, corrective therapies given, outcome and causality (ie, unrelated, unlikely, possible, probably and definitely). The responsible study clinician will assign the causality of the event. SAEs that are unexpected and are at least ‘possibly related’ to the study intervention will require expedited reporting within 24 hours of the in-country principal investigator or assigned representative becoming aware of it. This will be a maximum of 48 hours after the event occurred or the study team was made aware of the event (including the 24 hours required for the field staff to report to the principal investigator/representative). Additional information will be sent within 14 additional days (full SAE report) if the reaction had not resolved at the time of email notification.

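### Non-serious adverse events are identified by suspected relation to the product, and antibiotic use is also recorded at visits only the synbiotic arm has, so neither has a like-for-like comparator unless comparisons rest on the shared weekly morbidity contact

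*Protocol article*

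**What the plan says.** The Intervention section gives two sources for antibiotic data: "Antibiotic usage will be recorded during dosing visits and morbidity follow-up". It describes the dosing visits as follows: "Study staff will visit daily for 9 days after the initial dose and then weekly to age 6 months (32 doses in total". For the other arm it says: "Infants randomised to the control arm will receive the same follow-up as infants in the AASH observation cohort". No matching visits are described for controls.

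The morbidity route is common to both arms. Under Trial design, "Assessments of morbidity and breast feeding are conducted weekly up to 24 months of age", and the Outcomes section adds: "All infants will be followed up to 24 months of age with anthropometry, biological sample collections (blood, stool and saliva), and morbidity assessment". All infants also "will have contact details and mobile phone numbers of study staff for assistance in case of infant illness" (Intervention).

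Adverse events are covered at the end of Secondary outcomes: "Infants who develop adverse events that may be due to the study intervention will be identified by parents/carers", either by contacting staff or at follow-up visits. The same paragraph requires all serious adverse events (SAEs) to be reported, with no condition on cause at the first report.

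The Statistical analysis section plans to compare the proportion of infants with episodes of illness between arms at 1, 6 and 24 months. It names no between-arm comparison of antibiotic use or of adverse events.

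**The concern.** Two stated rules make the chance that an event is recorded depend on the arm.

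The first is the criterion for non-serious adverse events. It asks whether the event may be due to the product. In an open-label trial whose controls receive nothing, staff and carers know that a control infant's event cannot be. The same rash or loose stool is therefore eligible in one arm and not in the other. A table of such events by arm would show an excess on synbiotic by construction.

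The second is the extra source for antibiotic use. A course missed or forgotten at the weekly morbidity contact has a second chance of being recorded at a dosing visit, but only in the synbiotic arm. The imbalance is greatest in the first ten days.

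More recording in the treated arm works against a true reduction in illness or antibiotic use and can look like harm. The planned 1-month comparison of illness falls in the period when contact is most unequal, so it is exposed if illness noticed at a dosing visit is counted.

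**Working it through.** **1. Routes side by side**

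| Route or rule | Synbiotic | Control | Section |
|---|---|---|---|
| Weekly morbidity assessment to 24 months | yes | yes | Trial design, Table 1; Outcomes |
| Telephone contact with staff in illness | yes | yes | Intervention |
| Dosing visits, with antibiotic recording | yes, to 6 months | none | Intervention |
| Non-serious event must be possibly due to product | can be met | cannot meaningfully be met | Secondary outcomes |
| SAE reporting | all | all | Secondary outcomes |

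Only the third and fourth rows differ by arm.

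**2. Number of contacts**

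The plan's figure is 32 doses. The first dose plus 9 daily visits gives 10 daily doses, leaving 32 − 10 = 22 weekly ones. Staff visits after the first dose: 9 + 22 = 31. Weekly morbidity contacts to 6 months: 182 / 7 = 26 in each arm.

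- If dosing and morbidity visits are all separate: 26 + 31 = 57 contacts against 26.
- If each weekly dosing visit is also the morbidity visit: about 26 + 9 = 35 against 26.

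The article does not say which applies, so the excess is about 9 to 31. In the first 30 days there are 9 daily visits plus weekly ones at about days 17 and 24, so 11, compared with about 30 / 7 ≈ 4 morbidity contacts that both arms have. After 6 months the schedules are the same.

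The 22 weekly doses would end at about day 10 + 7 × 22 = 164 (5.4 months), whereas (182 − 10) / 7 = 24.6, so 24 would fit before 6 months. The total and the end date need reconciling, but this shifts the count by only two.

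**3. What unequal recording could do (illustration with assumed values)**

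The arm sizes come from Sample size determination and reproduce: with a difference of 0.2825 and SD 1.13, n = 1.5 × (1.96 + 0.84)² × (1.13 / 0.2825)² ≈ 1.5 × 7.85 × 16 = 188.4, so 189, and 378 in control.

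Assume the same true proportion p of infants with an event in both arms, recorded with probability s₁ (synbiotic) and s₀ (control). The apparent ratio is s₁ / s₀. With p₁ = p·s₁ and p₀ = p·s₀, the chance of a significant excess on synbiotic is

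Φ{ (p₁ − p₀ − 1.96·SE_pooled) / SE_unpooled }.

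For p = 0.20, s₁ = 0.90, s₀ = 0.70: p₁ = 0.18, p₀ = 0.14, SE_pooled = 0.0321, SE_unpooled = 0.0332, so (0.04 − 0.0629) / 0.0332 = −0.69 and Φ = 24.5%.

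| s₁ against s₀ (assumed) | Apparent ratio | p = 0.10 | p = 0.20 | p = 0.40 |
|---|---|---|---|---|
| 0.95 against 0.90 | 1.06 | 4.0% | 4.9% | 6.8% |
| 0.90 against 0.80 | 1.13 | 6.3% | 9.1% | 15.9% |
| 0.90 against 0.70 | 1.29 | 14.1% | 24.5% | 49.5% |

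The nominal rate in that direction is 2.5%. None of the recording probabilities or true proportions is in the document, so the table shows direction and sensitivity and does not estimate the bias.

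For non-serious adverse events no such model is needed: the control count is held near zero by the criterion itself.

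**The case against.** The strongest reply is that both arms already share an adequate route. Antibiotic use is also recorded at morbidity follow-up, which is weekly and covers every infant. Carers in both arms can telephone, and follow-up visits occur in both. Recording antibiotics at dosing visits has a purpose of its own, because the Intervention section asks for doses to be separated from antibiotics where possible. Nothing says that illness episodes are collected at dosing visits, and Table 1 names a weekly morbidity diary for them. All of this stands. A reader might infer that antibiotic use and adverse events are captured only in the synbiotic arm, or that planned comparisons are already distorted. The document supports neither: the shared route exists, and the only related comparison named is episodes of illness.

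SAEs are also better protected. All are to be reported, so any imbalance there is limited to staff perhaps hearing sooner of events in the arm they visit more often.

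A reader might go further and infer that the 12-month length is taken by the person who dosed the child, tilting the primary outcome. The phrase "including staff allocating newborns to the trial arms and laboratory staff analysing the biological samples" belongs to a sentence about concealing the allocation sequence from the rest of the research team. It does not say who measures length, and staffing is detail that an article may leave to the full protocol. No bias or error rate for length-for-age z-score can be drawn from that silence.

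What the reply does not answer is the adverse-event criterion, which depends on arm as written, and the absence of any statement that dosing-visit records stay out of between-arm comparisons.

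**Conclusion.** The point holds in a limited form. Non-serious adverse events, as defined, have no valid comparator. Antibiotic use has an additional recording source in one arm, amounting to about 9 to 31 extra visits by 6 months depending on whether weekly dosing and morbidity visits coincide. A spurious excess on synbiotic follows only if dosing-visit records are pooled into a comparison. The document neither plans nor excludes that pooling.

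The size of the bias is unknown. Under the assumed recording rates above, apparent ratios run from 1.06 to 1.29. Those figures rest on the assumptions that recording differs by arm, that there is no true effect, and that 189 and 378 infants are analysed. SAE reporting and the sample size are not in question, and the primary outcome is not affected by this ascertainment.

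**What to change.** 1. In the adverse-event paragraph, record all adverse events in both arms at the weekly morbidity contact, whatever the suspected cause, with the same questions and recall period. Assign causality afterwards. SAE reporting can stay as written.
2. State that every between-arm comparison of illness, antibiotic use and non-serious adverse events uses the weekly morbidity diary only.
3. Keep dosing-visit records for adherence, dose timing and the care of the individual infant. They may be listed descriptively for the synbiotic arm, labelled as having no control counterpart.

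The cost is a change of wording and a small change to the morbidity form, with no new visits and no effect on sample size. A few events seen only at dosing visits will leave the comparative tables, though they remain on record for safety oversight. Because the trial is open-label, carers who see staff more often may still report differently at the weekly contact. The fix makes the opportunity to report equal but cannot remove that.

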### Outcomes

All infants will be followed up to 24 months of age with anthropometry, biological sample collections (blood, stool and saliva), and morbidity assessment conducted at scheduled time points (table 1).

#### Primary outcome

The primary outcome of the trial is linear growth at age 12 months assessed by LAZ. Regularly calibrated equipment for anthropometry will include a Model 876 SECA/infant scale, UNICEF stadiometer/infantometer, Lufkin WP601 measuring tape and Holtain skinfold calliper. Measurements will be conducted in duplicate with a third measurement taken if the first two measurements do not agree within a specified amount. Weight will be recorded to the nearest 100 g and height, length, mid-upper arm circumference, head circumference, triceps and subscapular skinfolds, and knee-to-heel length to the nearest 0.1 cm. Measurements will be used to determine z-scores using the WHO growth standards for LAZ, weight-for-length (WLZ), triceps-for-age and subscapular-for-age. Children will be classified as stunted or wasted if their LAZ or WLZ is <−2 SDs, respectively.

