### Participants

Pregnant women recruited into the AASH observational study will be given an information sheet about this synbiotic trial at recruitment (online supplemental file 1). The women will be further approached by study staff at health facilities or in their homes within 3 days of delivery to determine whether their newborn meets the inclusion criteria and if she/he does, to obtain informed consent for participating in the SENGSYN trial (see online supplemental file 2)

10.1136/bmjpo-2022-001629.supp1Supplementary data

10.1136/bmjpo-2022-001629.supp2Supplementary data

Inclusion criteria are

Singleton newborn.BW or current weight (if BW not known) of ≥2000 g.Healthy infant who is breast fed and has taken at least one breastfeed well.Age 1–3 days.

Exclusion criteria are

Multiple birth (eg, twins, triplets, etc).Presence of any acute illness in the newborn (eg, fever and receiving treatment with antibiotics).Congenital abnormality that might be life-threatening or might impair growth.Infant with potential contraindication to synbiotic (eg, suspected immune suppression and cardiac abnormality).Mother unlikely to stay in study area for the duration of the trial.Any health- or study staff concerns regarding safety to participate in the trial.

Infants of women known to be HIV positive and without known immunosuppression are eligible to participate in the trial.

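### Skinfolds are recorded to the nearest 0.1 cm (1 mm), too coarse for the age z-scores derived from them; the 100 g weight step is coarse only in early infancy (minor)

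*Protocol article*

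**What the plan says.** All of the relevant text is in the Primary outcome section of the protocol article.

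- **Increments.** "Weight will be recorded to the nearest 100 g". Height, length and arm circumference share a single 0.1 cm rule with "head circumference, triceps and subscapular skinfolds, and knee-to-heel length to the nearest 0.1 cm".
- **Instruments.** Besides the scale and the length board, the section names the "Lufkin WP601 measuring tape and Holtain skinfold calliper". It gives no graduation for any instrument.
- **Use of the readings.** They yield "z-scores using the WHO growth standards for LAZ, weight-for-length (WLZ), triceps-for-age and subscapular-for-age". The section continues: "Children will be classified as stunted or wasted if their LAZ or WLZ is" below −2 SD.

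The primary outcome itself is LAZ at 12 months. The Secondary outcomes section lists stool, blood and saliva measures and contains no skinfold, weight or WLZ endpoint.

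**The concern.** One increment is used for measurements of very different size. A tenth of a centimetre is fine for a body length of tens of centimetres. For a skinfold of a few millimetres it is a large part of the variation between infants, and that variation is what an age z-score expresses. Precision lost at data entry cannot be recovered afterwards.

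Weight raises a weaker form of the same question. A 100 g step is a larger share of the spread of weight at a given length in a young infant than in an older child, and weight feeds both WLZ and the wasted class.

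What is at stake is the precision of the skinfold-for-age z-scores and of the earliest WLZ values, not the main comparison of the trial.

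**Working it through.** **1. Is the primary design affected?** The Sample size determination section gives a control mean LAZ of −1.13, SD 1.13, a 25% improvement, 80% power, α = 0.05 and 1:2 allocation. The difference is 0.25 × 1.13 = 0.2825. Taking α as two-sided, the intervention arm needs (1 + 1/2) × (1.960 + 0.842)² × (1.13/0.2825)² = 1.5 × 7.85 × 16 ≈ 188.4, so 189, with 378 controls. This matches the plan. Dividing by 0.8 gives 236.25 and 472.5, against the plan's 236 and 472. None of these inputs involves skinfolds or weight. LAZ needs length only: with an assumed length SD of 2.4 cm, the largest rounding error is 0.05/2.4 ≈ 0.02 z. The 0.1 cm rule is adequate there.

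**2. Method for rounding.** Treat the z-score as linear in the reading, and the rounding error as uniform over a step h. The largest error is h/2, the error variance is h²/12, and the proportional rise in variance is (h²/12)/SD². The documents give no SD for skinfolds or for weight at a given length, so **every SD below is an assumption**.

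**3. Skinfolds, h = 1 mm (error variance 1/12 = 0.083 mm²).** The last column is the power for an illustrative 0.25 SD difference at 189/378. It is 80.1% without rounding. The plan sets no such target for skinfolds.

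| Assumed SD | One step | Largest error | Variance rise, single reading | Power |
|---|---|---|---|---|
| 1.0 mm | 1.00 z | 0.50 z | 8.3% | 76.9% |
| 1.25 mm | 0.80 z | 0.40 z | 5.3% | 78.1% |
| 1.5 mm | 0.67 z | 0.33 z | 3.7% | 78.7% |
| 2.0 mm | 0.50 z | 0.25 z | 2.1% | 79.3% |

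If duplicates were averaged and their rounding errors were independent, the variance rise would halve to about 1.0-4.2%. Two close readings often round the same way, so the full halving cannot be counted on.

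**4. Weight, h = 100 g (largest error 50 g).**

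| Assumed SD of weight at given length | Largest error | Variance rise |
|---|---|---|
| 200 g (near birth) | 0.25 z | 2.1% |
| 300 g (near birth) | 0.17 z | 0.9% |
| 600 g (later) | 0.08 z | 0.2% |
| 1000 g (later) | 0.05 z | 0.1% |

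The wasted class was simulated with mean WLZ between −0.5 and −1.0. Rounding moves 1.3-2.4% of children across −2 at an SD of 250 g, and 0.4-0.8% at 800 g. Movements in the two directions nearly cancel, so estimated prevalence shifts by less than 0.2 percentage points in either case.

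**5. What finer recording would give.** For illustration, a skinfold step of 0.1-0.2 mm would bring the largest error down to 0.025-0.10 z over the same SDs. A weight step of 10 g would bring it to 0.025 z or less.

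**The case against.** The strongest reply is that nothing the trial tests depends on these measurements. LAZ uses length, and no skinfold, weight or WLZ endpoint is in the secondary list. At group level the loss is modest, because the figures of 0.25-0.50 z are worst cases for one reading. The sentence may also be a units slip or a condensation, since it strings lengths, circumferences and skinfolds together in centimetres and fuller procedures are held elsewhere. All of this stands as a limit on severity. It does not remove the point: the article states the increment explicitly, so this is a rule fixed badly and not a detail left out, and the article commits the trial to deriving these z-scores.

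Three stronger readings are tempting, and the documents do not support them.

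- **Entry limit.** A reader might infer that an infant of 1950-1999 g would be recorded as 2000 g and enrolled. The criterion in the Participants section is "BW or current weight (if BW not known) of ≥2000 g". Birth weight comes first, no precision is given for either weight, and nothing says that the 100 g step in the Outcomes section governs screening.
- **Duplicate check.** A reader might infer that rounding blunts the repeat rule: "Measurements will be conducted in duplicate with a third measurement taken if the first two measurements do not agree" within a set amount. That amount is not shown, and the article does not say that agreement is judged on rounded values.
- **Calliper resolution.** A reader might say that most of the instrument's resolution is thrown away. The calliper is named, but its graduations are not in the document, so the size of that loss cannot be stated.

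**Conclusion.** The point holds as a minor one. As written, skinfolds are recorded in steps worth 0.5-1.0 z, with a largest rounding error of 0.25-0.50 z and about 2-8% added variance for a single reading, if the between-infant SD is 1.0-2.0 mm. That is too coarse for an individual skinfold-for-age z-score and a small loss of precision for a comparison of arms.

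The weight step matters for WLZ only in early infancy, at about 0.17-0.25 z if the SD of weight at a given length is 200-300 g. Later it adds roughly 0.1-0.2% to the variance.

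A reader might infer from this that the treatment comparison is biased or the trial underpowered. Neither follows. The increment is the same in both arms, so rounding adds noise. The primary outcome, the sample size and the listed secondary outcomes do not use these readings.

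**What to change.** Give separate increments in the anthropometry text:

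- skinfolds in millimetres, to the smallest graduation of the calliper;
- weight to the smallest increment the scale displays;
- no further rounding of either at data entry;
- 0.1 cm kept for length, height and circumferences.

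If the forms already hold skinfolds in finer units and 0.1 cm is a slip in the article, correct the unit and nothing else for skinfolds.

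The cost is one sentence and the matching data-entry fields. Equipment, staff, visits and sample size stay as they are.
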